## Objective

2

The study aims to verify the hypothesis that the concurrent use of CMT or acupuncture treatment with pregabalin, a medication commonly used for CIPN is more effective and safe for the relief of CIPN symptoms than is pregabalin-alone therapy.

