#### Secondary outcome

3.8.2

Secondary outcome assessment measures the change and rate of change in the Quality of Life Questionnaire-CIPN 20-Item Scale (EORTC QLQ-CIPN 20) and Quality of Life questionnaire (EORTC QLQ-C30, version 3.0) developed by the European Organisation for Research and Treatment of Cancer in comparison to the baseline.^[22–24]^ EORTC QLQ-CIPN 20 consists of 20 questions, with 9 sensory nerve-related questions, 8 motor neuron-related questions, and 3 autonomic nerve-related questions. A higher score indicates a more severe degree of peripheral neuropathy.^[22]^ EORTC QLQ-C30 is a tool for measuring health-related quality of life and consists of 2 items of the overall functional state, 15 items of function, and 13 items of symptoms. A lower overall score indicates a better quality of life.^[25]^

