### Statistical analysis

3.9

All statistical analyses will be conducted by a blinded professional statistician. All participants who provided written consent and were assigned a screening number for the study are included in the screening set, and patients randomized to the treatment group are included in the randomized set. Intention-to-treat (ITT) analysis will be performed in patients who have received at least one pregabalin trial or at least one session of acupuncture or CMT. Per-Protocol Set (PPS) analysis will be performed in patients who meet the inclusion/exclusion criteria, have no significant conditions affecting the efficacy assessment, show > 80% treatment compliance, and have performed at least one evaluation after the baseline evaluation.

The statistical analysis for the efficacy evaluation, based on ITT analysis and PPS analysis are conducted in parallel. All statistical tests will be performed as two-sided tests with a significance level of 5%, and two-sided 95% confidence intervals. Primary outcome assessments are performed with ANOVA analysis to test the differences between the groups for changes in FACT/GOG-NTX at the end of week 5, compared to baseline. If the differences between groups are significant, the Tukey method will be used. For secondary outcome evaluation, continuous variables are analyzed with ANOVA analysis or Kruskal–Wallis test, and categorical variables are analyzed with Pearson's chi-squares test or Fisher's exact test. The Exploratory Efficacy assessment will summarize the descriptive statistics on the chemotherapy completion rate, followed by the appropriate statistical analysis.

For the occurrence of adverse events, the number of cases, number of participants, severity, and causal relationship with the investigational drug can be statistically analyzed by group, and nonparametric methods can be applied as needed. The results of vital signs, physical examination, electrocardiograms, and laboratory tests will be reviewed in a comprehensive manner, and statistical analysis will be conducted as necessary for the test items deemed clinically significant by the investigators. Depending on the nature of the data, continuous data will be summarized by observed values, mean, standard deviation, median, minimum, and maximum for each visit, and categorical variables will be summarized by frequency and percentage.

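### The test named for the continuous secondary scales is a three-group comparison that does not itself estimate either add-on against pregabalin alone, and it leaves out baseline score and cancer type

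*Protocol article*

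**What the plan says.** Section 2 (Objective) of the protocol article sets out to show that adding CMT or acupuncture to pregabalin "is more effective and safe for the relief of CIPN symptoms than is pregabalin-alone therapy". That is two comparisons, each with pregabalin alone as reference.

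Section 3.8.2 defines the secondary outcomes: "Secondary outcome assessment measures the change and rate of change in the Quality of Life Questionnaire-CIPN 20-Item Scale", and likewise for the QLQ-C30.

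Section 3.9 (Statistical analysis) treats the two outcome levels differently:

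- Primary: "Primary outcome assessments are performed with ANOVA analysis to test the differences between the groups for changes in FACT/GOG-NTX", followed by "If the differences between groups are significant, the Tukey method will be used".
- Secondary, in the next sentence: "For secondary outcome evaluation, continuous variables are analyzed with ANOVA analysis or Kruskal–Wallis test". No pairwise step follows.

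The same section says in general terms: "All statistical tests will be performed as two-sided tests with a significance level of 5%, and two-sided 95% confidence intervals". It does not say which differences the intervals are for. It also plans means, standard deviations, medians and ranges at each visit. Section 3.6 stratifies randomization by breast or colorectal cancer. No analysis in section 3.9 uses that factor.

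**The concern.** A three-group test combines three differences: EA versus pregabalin, CMT versus pregabalin, and EA versus CMT. The objective asks for the first two only. A significant result can be driven largely by the third, and a Kruskal–Wallis test on its own gives no estimate to which an interval could be attached. A pilot's secondary results are most useful as estimates of each add-on against the control, for planning a later trial, and the named method does not itself produce them.

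The second part is precision. In an analysis of change scores the baseline enters only by subtraction. Adjusting for it as a covariate generally gives tighter comparisons, and the stratification factor is available at no cost.

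**Working it through.** **Inputs.** Section 3.3 gives 30 per group and a 20% dropout assumption. Section 3.6 gives three arms at 1:1:1. Section 3.9 gives a two-sided 5% level. The article states no effect size, standard deviation or correlation, so those below are assumptions, shown as ranges.

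**The plan's own figure.** 3 × 30 = 90 reproduces the stated total. After dropout, 30 × (1 − 0.20) = 24 per arm, which is used below.

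**1. What the overall test responds to.** The power of the F test depends on the true arm means μ₁, μ₂, μ₃ (in SD units) only through λ = n × Σ(μᵢ − μ̄)². With n = 24 and means in the order pregabalin, EA, CMT:

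- Both add-ons help, (0, 0.5, 0.5): μ̄ = 0.333, Σ = 0.111 + 0.028 + 0.028 = 0.167, λ = 4.0.
- Only EA helps, (0, 0.5, 0): μ̄ = 0.167, Σ = 0.028 + 0.111 + 0.028 = 0.167, λ = 4.0.
- Opposite signs, (0, 0.3, −0.3): μ̄ = 0, Σ = 0.09 + 0.09 = 0.18, λ = 24 × 0.18 = 4.32.

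The test is about equally likely to be significant in all three, although they mean very different things for the objective.

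**2. How often a significant overall test comes with no difference from pregabalin.** Simulated trials with normal data, SD 1 and 24 per arm. Share of significant F tests in which neither add-on differs from pregabalin by a two-sided t-test at 5%:

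| Assumed effects (EA, CMT), SD | Share |
|---|---|
| +0.8, +0.8 | under 0.1% |
| +0.5, +0.5 | under 1% |
| +0.8, +0.4 | about 1% |
| +0.6, +0.3 | about 3% |
| +0.8, 0 | about 8% |
| +0.5, 0 | about 16–17% |
| +0.3, −0.3 | about 31% |

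In the last row the F test itself is significant in 43% of trials. If the follow-up is Tukey instead of unadjusted t-tests, the shares are larger: about 2% (+0.8, +0.8), 19% (+0.8, 0) and 53% (+0.4, −0.4).

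**3. What baseline adjustment gains.** Let baseline and follow-up each have variance σ² and correlation ρ.

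- Change score: variance 2σ²(1 − ρ).
- Follow-up adjusted for baseline: variance σ²(1 − ρ²).
- Ratio, adjusted to change: (1 + ρ)/2.

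At ρ = 0.3 the ratio is 0.65, a 35% cut. At ρ = 0.5 it is 0.75, a 25% cut. At ρ = 0.7 it is 0.85, a 15% cut. Interval width scales with the square root: √0.65 = 0.81 and √0.85 = 0.92, so intervals are about 8–19% narrower. In terms of participants, 24 per arm then does the work of 24/0.85 ≈ 28 to 24/0.65 ≈ 37 per arm analysed on change scores. The cost is two degrees of freedom (one for baseline, one for cancer type) out of 3 × 24 − 3 = 69.

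The further gain from adjusting for cancer type cannot be computed, because the article does not say how strongly the scales differ between the two cancers.

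**The case against.** The strongest reply is that this is a condensed article. The full protocol and any analysis plan are not shown, and a follow-up procedure for secondary outcomes is the kind of detail left to them. Silence on a pairwise step does not rule one out, and the Tukey sentence is not expressly confined to the primary outcome, although its position makes that the natural reading. This stands as far as it goes: the absence of a post-hoc rule alone would be no error. What remains is that the article does name a method for these scales, and the named method does not target the article's own objective.

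A reader might infer that a significant secondary result could not show whether EA or CMT helped. The documents do not support that. Confidence intervals are planned in general, and group summaries at each visit would show the direction and rough size of each difference from pregabalin.

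A reader might also infer that leaving ANOVA or Kruskal–Wallis open invites choosing the more favourable p-value. That is too weak to carry the point. The paired wording is common shorthand for parametric or nonparametric according to distribution, as in the parallel phrase "categorical variables are analyzed with Pearson's chi-squares test or Fisher's exact test". The rule for choosing is ordinary analysis-plan detail, and section 3.9 assigns the analysis to a blinded statistician. Even deliberate picking raises a 5% error rate only to about 6% with normal data, and to no more than 7% in the skewed and heavy-tailed cases tried.

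Finally, the 31% figure comes from a pattern in which one add-on harms as much as the other helps. Under the trial's own hypothesis that both help, the share is about 0–3%. That is correct, and it is why a range is given.

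**Conclusion.** The point holds in a limited form. For QLQ-CIPN20 and QLQ-C30 the only method named is a three-group test. It does not by itself estimate either comparison in the objective, and it leaves out the baseline score as a covariate and the stratification factor.

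The mismatch matters little if both add-ons help about equally. It is moderate if only one does (8–17% for effects of 0.8 down to 0.5 SD), and largest if they pull in opposite directions (31% at ±0.3 SD). The 15–35% variance reduction assumes equal variances at baseline and follow-up and a correlation of 0.3–0.7. None of these effects or correlations comes from the article. As these are secondary outcomes of a self-described pilot, the change is desirable, not essential.

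**What to change.** In section 3.9, replace the sentence on continuous secondary outcomes with a statement that, for each secondary scale score, EA minus pregabalin and CMT minus pregabalin will be reported with 95% confidence intervals. Both come from one linear model with treatment group, baseline score and cancer type, and are reported whatever the overall three-group test shows. Keep Kruskal–Wallis as a named sensitivity check.

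The cost is a sentence of wording and slightly more reporting. Baseline scores and cancer type are already collected, so no new data, visits or participants are needed.

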#### Quality control and data monitoring

3.9.1

This study will be monitored by CROCENT Co., Ltd., a CRO company that consults with institutions conducting clinical trials to ensure compliance with protocol and K-GCP. During monitoring, crosschecks will be made with the evidence to ensure that the documents (trial master files, CRF, informed consent forms, and adverse events reports) are complete and clear.

### Ethics and dissemination

3.10

#### Research ethics approval

3.10.1

This trial has received complete ethical approval from the Ethics Committee of Catholic Kwandong University International St. Mary's Hospital (IS18ENSI0054).

#### Protocol amendments

3.10.2

The investigators who want to protocol amendments should first discuss it with the principle investigator, and they can change the protocol after obtaining approval from the IRB. However, when a dangerous situation occurs and immediate care is needed, the protocol change will be reported to the IRB at a later time.

#### Post-trial care

3.10.3

If the patients experience unexpected accidents or injuries, the patients will receive appropriate medical care at the Catholic Kwandong University International, St. Mary's Hospital. Additionally appropriate compensation will be made by the insurance company, according to the patient compensation rules of the trial.

## Discussion

4

Through sampling analysis of Health Insurance Review and Assessment Service (HIRA) data on Korean medicine (∼1 million persons, conducted on January 15, 2018), the analysis on prescription frequency of CIPN as primary disease and secondary disease for 10 years showed no reported case, indicating that currently, there has been no approaches in terms of Korean medicine treatment of CIPN in the corresponding clinical studies.^[26]^

Korea has the world's highest incidence of colorectal cancer. In addition, the number of breast cancer patients in Korea increased four times from 3801 in 1996 to 16,398 in 2010 and is in the trend of steady increase.^[27]^ Especially, colorectal cancer and breast cancer have high incidence rates and have a long treatment period compared to other types of cancers, during which the patients can experience multiple side effects of chemotherapy including CIPN.

This study will be conducted to evaluate the efficacy and stability of combining conventional treatment and complementary alternative treatment (oriental medicine) for CIPN induced by anticancer drugs used for patients with colorectal cancer and breast cancer based on various evaluation indices. We believe that this study will be instrumental in providing better alternative solutions to CIPN, a refractory disease and overcome the limitations of existing studies, despite its own limitations.
